**Fig. 1 Fig1:**
[figure not shown]
Participant Pathway

#### Inclusion criteria for entry to the pre-randomisation phase

Currently under the care of secondary care mental health services at screening with a plan for the patient to remain in secondary care throughout the period of the trial.A decision made by the patient’s clinical team that a change in medication is indicated.A current diagnosis of Bipolar Disorder (type I or II), defined as in Diagnostic and Statistical Manual of Mental Disorders-5 (DSM-5) [54], which is supported by the use of the Mini-International Neuropsychiatric Interview (MINI) [55].Currently depressed, i.e. meeting DSM-5 criteria for a Major Depressive Episode assessed via MINI and with a current Quick Inventory of Depressive Symptomology – Self Report (QIDS-SR) > 10 [33, 54].Current episode of depression failed to have responded to adequate trials, or lack of tolerability or patient declined/clinically inappropriate, of two different NICE recommended medications (quetiapine, olanzapine with or without fluoxetine, lamotrigine) or lurasidone. Adequacy of treatment trial defined using a custom designed ‘Bipolar Demographics and Treatment Questionnaire’ (BDTQ).Aged 18 or over at the point of consent.Willing and able to provide written informed consent prior to any trial procedures taking place.In the opinion of the investigator, is able to follow the trial prescription instructions and is able to manage 8 weeks supply of trial medication without risk of overdose.The patient, if female and of child-bearing potential, must have a negative pregnancy test [urine beta-human chorionic gonadotropin (β-hCG)].Women of child-bearing potential are required to use a highly effective contraceptive method during the pre-randomisation and post-randomisation phase of the trial. Highly effective methods of contraception include:
combined (oestrogen and progestogen containing) hormonal contraception associated with inhibition of ovulation (oral, intravaginal, transdermal)progestogen only hormonal contraception associated with inhibition of ovulation (oral, injectable, implantable)intrauterine deviceintrauterine hormone-releasing systemvasectomised partner (provided that partner is the sole sexual partner of the trial participant and that the vasectomised partner has received medical assessment of the surgical success)bilateral tubal occlusionsexual abstinence (defined as refraining from heterosexual intercourse during the entire period of risk associated with the study treatments. The reliability of sexual abstinence needs to be evaluated in relation to the duration of the clinical trial and the preferred and usual lifestyle of the subject)

#### Exclusion criteria for the pre-randomisation phase

DSM-5 defined severe substance use disorder.Current psychotic symptoms as assessed using the MINI.History of retinal disease.Current cardiovascular symptoms or significant concerns around cardiovascular disease.History of significant renal disease (for example within the last 6 months estimated Glomerular Filtration Rate (eGFR) is less than 50 ml/min/1.73 m2 or there is a concern that eGFR is deteriorating and may be expected to fall below 50 during the course of the study).Any known sensitivity to trial drug including its excipients.Current pregnancy or planned pregnancy during the trial period, or breastfeeding.Starting specific psychotherapy from four weeks before randomisation through to Week 12 post-randomisation.Currently taking part in another clinical trial that would interfere with the outcomes of PAX-BD.Confirmed diagnosis with potential confounding factors such as Parkinson’s disease, restless leg syndrome (where restless legs syndrome has been formally diagnosed by a sleep clinic).Significant clinical concern regarding impulse control behaviours.

#### Inclusion for randomisation

All criteria as for the pre-randomisation plus:
Been in pre-randomisation for a minimum of 23 calendar days.Severity of depression still meeting the criteria of QIDS-SR > 10.A minimum of two telephone phone calls with a trial RA and two on-line weekly symptom ratings have been completed during the pre-randomisation phaseOn mood stabilising medication (lithium, valproate, carbamazepine, lamotrigine)If on an antipsychotic this must be one listed, and at a dose of no more than the maximum stated in Table 2.All regular psychotropic medication, including antipsychotics and mood stabilisers, at a stable dose for a minimum of four weeks. Additionally, if a participant is on lamotrigine, quetiapine, olanzapine or lurasidone then this must have been at the current dose or higher for a minimum of three months.

#### Exclusion criteria for randomisation

As for the pre-randomisation phase plus:
Psychotic symptoms over the preceding 4 weeks.Any deterioration in physical or mental health since pre-randomisation that means there is a clinical concern to proceed with the study.Any study team’s concern regarding the patient’s ability to remain engaged in the study collecting self-ratings of their symptoms.

### Intervention

Participants are randomised on a 1:1 basis to receive either pramipexole or placebo. Dosing of study medication is based on doses used in the two previous small pilot studies (*n* = 22; *n* = 21) [30, 31] and, in particular, a naturalistic case series [24]. Dosing occurs in three phases: titration, fixed dose and flexible dose phases. During the titration phase, participants start on a dose of 0.25 mg/daily with 0.25 mg increments every three days to reach the maximum tolerated dose, with a maximum of 2.5 mg/daily, over four weeks. The dose achieved in the titration phase is continued through the fixed-dose phase between weeks 5 to 12 post randomisation. From week 12 to the end of the study, medication is flexibly dosed between 0.25 and 2.5 mg/day, based on the participant’s trajectory of change in mood and tolerability as judged by self-reported measures and side effects.

At 48 weeks, remaining participants are asked whether they wish to continue with pramipexole after the trial if they are found to be taking it; those who do are unblinded to find if they were receiving the drug or placebo. This allows for the immediate withdrawal of participants on placebo, and the continuation of treatment for those receiving pramipexole beyond the study. Participants who wish to discontinue study medication are not unblinded and receive a tapering schedule of a reduction by 0.25 mg every three days, to safely withdraw from trial medication.

Participant’s clinical teams are free to adjust all other medication, though encouraged wherever possible to maintain stability of all medication and doses between randomisation and the 12 week primary outcome point. Participants are provided study diaries at the start of randomisation to guide them through the titration phase, record the dose of medication taken each day, record any changes to concomitant medication and record AEs (Supplementary files 10 and 11). Adherence to the dose schedule is verbally checked with the participant during RA telephone calls.

AEs are recorded by trial RAs for all participants from the date of consent to the pre-randomisation phase until the participant’s final trial assessment, or until participant withdraws. AEs are recorded on the trial’s MACRO™ system by the trial RAs. Line listings of all AEs for a participant are sent to the site PI or delegated clinician for assessment of seriousness, severity and causality. Serious Adverse Events must be reported within 24-h by all staff members as soon as they become aware of the event.

#### Randomisation and blinding

Sealed Envelope, a secure web-based system managed centrally is used to randomise participants with concealed allocation. The first 10 participants are allocated randomly. Subsequently, a non-deterministic minimisation algorithm is used with an 80% bias in favour of allocations that minimise an imbalance on variables hypothesised to be related to prognosis at baseline: bipolar I or bipolar II based on DSM-5 criteria; severity of depression at randomisation (moderate, severe or very severe); age (18–50 or > 50); biological sex (male or female); UK site region (North, Midlands and East, London, South East, South West, Scotland, Wales or Northern Ireland); concurrent mood stabiliser (lithium, valproate, lamotrigine, carbamazepine or multiple mood stabilisers); concurrent antidepressant (yes or no); on an antipsychotic at randomisation (yes or no); number of mood episodes in the past year (< 4 or ≥ 4).

Pramipexole and matching placebo are manufactured by Wasdell then packaged and labelled by Modepharma. Trial medication is then delivered blinded to the CNTW pharmacy for storage and dispensing. The TMG is blind to treatment allocations. An unblinded Data Manager will provide the DMC the key to unblind treatment arms for closed reports. To prepare these reports, a trial statistician is partially blinded and provided data by the unblinded Data Manager where treatment arms are coded as A and B. Participants and staff at recruitment sites remain blinded for the duration of the study, though unblinding can occur in the event of a clinical emergency.

### Data handling

Data is handled, computerised and stored in accordance with the Data Protection Act 2018. Paper copies of trial related documentation are annotated, signed and dated, and filed in the medical notes. The overall quality and retention of trial data is the responsibility of the Chief Investigator (CI). All trial data is retained in accordance with the latest Directive on GCP (2005/28/EC) and local policy.

Clinical and safety data for trial participants is collected by site staff and trial RAs, and recorded in the electronic case report form (eCRF) of the clinical data management system MACRO™ and password protected trial spreadsheets. Unique trial identifier numbers are used for participant identification on the eCRFs and trial spreadsheets.

Primary outcome data, in the form of answers to all trial questionnaires (Health Economic and otherwise) are entered directly by the trial participants into the University of Oxford True Colours online platform. Participants receive login details in the form of a username and password at the start of the trial, and change their password to something only they know.

### Statistical analysis

Full details of all statistical analyses will be specified in a pre-defined Statistical Analysis Plan. Initial descriptive analysis will present the profile of the participants and investigate differences in demographic and outcome measures between the two treatment arms at baseline. If significant differences are found, the variable may be added to the models testing the relevant study hypothesis. A two-sided significance level of *p* < 0.05 will be used throughout.

Analysis of the primary outcome measure of QIDS-SR [33] at week 12 will use Analysis of Covariance (ANCOVA) to examine the difference between the treatment arms with adjustment for baseline covariates including initial QIDS-SR score, other minimisation factors and anxiety (GAD-7) score [35]. Other baseline covariates will be examined for potential inclusion during the modelling process.

Weekly repeated measures scores for QIDS-SR [33] will be examined to ascertain participant compliance in completion. Should this be judged sufficient, a mixed effects linear regression model will be used to account for the repeated measures over time in comparing this outcome between the treatment groups. Other secondary outcome measures include: the proportion of participants in remission at 12 and 48 weeks (QIDS-SR score ≤ 5), the proportion of participants who have achieved a response at 12 and 48 weeks (QIDS-SR score reduction of ≥50% from baseline), proportion of time over 48 weeks that participants are free of depressive symptoms (QIDS-SR score ≤ 5), proportion of time over 48 weeks that participants are free of manic symptoms (ASRM score ≤ 5) and changes in psychosocial function determined by the WSAS (35;37;42).

Secondary outcomes, other than those collected specifically for the health economic analysis, will be analysed in a similar manner to the primary outcome as described above. The ASRM and GAD-7 scores will also be examined on a weekly basis as described for the QIDS-SR [33–35]. MADRS, YMRS, SHAPS and QIDS-C between 0 and 12 weeks will be examined in a manner analogous to the primary analysis of the primary outcome [33, 36–38]. Safety and tolerability assessments will include ANCOVA of TSQM and QUIP-RS scores [40, 41], co-varying for baseline score and GAD-7 anxiety scores [35] given the impact of anxiety on tolerability and reported side effects with medication.

Levels of missing data will be described and baseline values tabulated for those for whom the primary end point can and cannot be calculated in order to summarise any characteristics related to missingness. Data with missing observations due to participant withdrawal or loss to follow-up will be examined to determine both its extent and whether it is missing at random. It is likely that missingness will be related to the outcome itself with depressed participants less likely to complete assessments. However, it has been suggested that even when non-random, a valid approach is to assume randomness since results tend to remain stable when randomness is violated. The primary analysis will utilise complete case analysis with covariate adjustment. This yields similar results to multiple imputation in data that are missing randomly, as long as predictors of missingness are included. If data are missing to a sufficient extent (e.g. between approximately 10 and 20%), the use of appropriate multiple imputation techniques will be considered. The QIDS-SR [33] is assessed weekly. For the primary analysis, the assessment closest to 12 weeks in the range 10–14 weeks will be employed. Missing items from a partially completed TQSM questionnaire [41] will be handled as described in the scoring manual.

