### Sample size, power and effect size

The estimated sample size for randomisation is based on the CEQUEL study [32] that included similar participants in a depressive episode of BD from the UK NHS, and who had weekly remote monitoring of mood over a 52 week period. Dropout rates in this study were 20% at 12 weeks and 50% at 52 weeks. A power calculation demonstrates that 290 participants provides a 90% power of detecting a 3-point difference in QIDS-SR [33] between pramipexole and placebo (*p* < 0.05), based on a two-sample t-test at 12 weeks with a QIDS-SR [33] standard deviation of 7 and assuming a 20% dropout rate as seen in the CEQUEL study [32]. This sample size also provides approximately 80% power of detecting a 3.3 point difference in QIDS-SR scores [33] between the treatment arms at week 48 assuming the 50% dropout rate seen in CEQUEL [32] and the standard deviation used above. In a study of a similar population, a drop-out rate of 30% was experienced during the pre-randomisation phase [46]. As a result, it is anticipated that PAX-BD will need to recruit approximately 414 participants into the pre-randomisation phase trial to achieve the target of 290 participants randomised.

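### The primary ANCOVA covariate set is left open to baseline significance tests and to choices made while modelling; it should be closed before outcomes are seen by arm

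*Protocol article*

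**What the plan says.** All of the analysis text is in the protocol article, section Statistical analysis.

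- The primary analysis is an ANCOVA of QIDS-SR at week 12. The covariates named are baseline QIDS-SR, the other minimisation factors and GAD-7. They are introduced as examples of the adjustment set, not as the whole of it.
- The opening paragraph plans a comparison of demographic and outcome measures between arms at baseline, and continues: "If significant differences are found, the variable may be added to the models testing the relevant study hypothesis".
- The paragraph on the primary outcome ends: "Other baseline covariates will be examined for potential inclusion during the modelling process".
- On the error rate: "A two-sided significance level of *p* < 0.05 will be used throughout".
- The section promises a pre-defined statistical analysis plan. Nothing in the article withdraws or limits the two sentences on adding covariates.

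**The concern.** The two sentences are two separate routes into the model. The first is triggered by a significance test on a baseline difference and is optional. The second has no trigger at all. Neither has a candidate list, a selection criterion or a condition on who may see what when the choice is made.

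The first route uses the wrong criterion. Allocation is randomised and minimised on nine factors (section Randomisation and blinding). A significant difference in any other baseline variable is therefore due to chance. The test does not show whether the variable predicts the outcome, and that is the valid reason to adjust. The plan already has a set chosen on that ground, because it describes the minimisation factors as thought to relate to prognosis.

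The second route places the choice at a time when outcome data are in use. If several adjusted models are fitted and one is reported, the stated 5% level describes the test only if the choice did not depend on the treatment estimate. Nothing in the article ensures that. A primary result near p = 0.05 could be disputed whichever model was reported.

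**Working it through.** **1. The plan's own figure.** Inputs from section Sample size, power and effect size: "A power calculation demonstrates that 290 participants provides a 90% power of detecting a 3-point difference in QIDS-SR", "based on a two-sample t-test at 12 weeks", with "standard deviation of 7 and assuming a 20% dropout rate as seen in the CEQUEL study". Allocation is 1:1 (section Intervention).

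- n per arm = 2(1.960 + 1.282)² × 7² / 3² = 2 × 10.51 × 49 / 9 = 114.4, so 115 per arm and 230 in total.
- Allowing for dropout: 230 / 0.80 = 287.5, so 288, against 290 stated. The figure is reproduced.
- 290 × 0.80 = 232 evaluable, or 116 per arm. Power by the t-test is 90.2%.

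This sizing is unadjusted, so it does not depend on the covariate list.

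**2. How often the baseline test would fire by chance.** For k independent tests at 0.05, the chance of at least one significant result is 1 − 0.95^k. The article does not give k, so a range is shown.

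| k | 5 | 10 | 15 | 20 |
|---|---|---|---|---|
| Chance of at least one | 23% | 40% | 54% | 64% |

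This is the chance that the rule is triggered. It is not a type I error rate.

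**3. Type I error under each way of using the rules.** ANCOVA was simulated with no treatment effect, 232 evaluable participants in equal arms and 8,000 runs per setting. The base model had treatment and one baseline covariate correlated 0.5 with the outcome. K extra candidates, independent of one another, jointly explained a share R² of the residual variance. K, R² and the 0.5 are assumptions, and the minimisation factors were not modelled. Simulation standard error near 5% is √(0.05 × 0.95 / 8,000) = 0.0024.

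| Model used | K=5, R²=10% | K=5, R²=30% | K=10, R²=10% | K=10, R²=30% |
|---|---|---|---|---|
| Fixed base model | 0.0492 | 0.0503 | 0.0476 | 0.0539 |
| Add every covariate with baseline p < 0.05 | 0.0472 | 0.0408 | 0.0452 | 0.0470 |
| Add covariates correlated with outcome (p < 0.05) | 0.0515 | 0.0494 | 0.0488 | 0.0546 |
| Smaller p-value, with or without the flagged covariates | 0.0529 | 0.0536 | 0.0524 | 0.0600 |
| Smallest p-value over models with none, one or all extras | 0.0816 | 0.1036 | 0.0832 | 0.1121 |

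The baseline test fired in 22 to 23% of runs with K = 5 and in 41% with K = 10, in line with step 2.

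**4. Cross-check with another set of candidates.** With 232 evaluable and eight candidates each correlated 0.2 or 0.15 with the outcome, forward selection on the covariates' own significance gave 4.9% and 5.6% (2,500 runs). Taking the smallest treatment p-value over no addition or one addition gave 8.6% and 8.1% (3,000 runs).

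**5. Reading.** Mechanical use of the baseline test lies below the fixed model in all four settings. Selection on prognosis is nominal. Clear inflation appears only in the last row, where the treatment p-value itself guides the choice.

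**The case against.** **The analysis plan may settle this.** The article defers full detail to a pre-defined plan that is not shown, and both sentences are permissive, so that plan could close the list. This stands as a possibility. But the article does not merely leave out detail. It states a selection rule, and an analysis plan that followed it would carry the rule forward.

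**The rule does not inflate the error.** For the baseline-test sentence used mechanically, this is right. A reader might infer that the 5% test fails outright, or that covariates would be added one after another to shrink the treatment p-value, with still larger inflation. The documents do not support either inference: they allow discretion but nowhere say that covariates are chosen by the treatment result.

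**The person choosing may not see outcomes by arm.** A reader might infer the opposite from the statement that "a trial statistician is partially blinded and provided data by the unblinded Data Manager where treatment arms are coded as A and B". That sentence concerns the preparation of closed reports for the Data Monitoring Committee. Nothing says that this statistician selects the primary model, so the point does not rest on it.

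**Further covariates may be needed.** The plan's primary analysis is complete-case, and the plan justifies this on condition that variables predicting missing data are in the model. Some may not be known yet. This stands, and it shapes the fix. It supports naming such variables in advance, and it is not a reason to admit covariates on baseline significance.

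**The core set is already named.** True, and it limits how far extra covariates can move the estimate. That bears on severity.

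**Conclusion.** The concern holds in limited form. The plan states a poor selection rule and leaves the primary model open, with no point at which it must be fixed. Type I error is about 4.1 to 4.7% if the baseline test is applied mechanically, about 5% if covariates are selected on association with outcome, and roughly 8 to 11% if the choice among models follows the treatment result. The last range assumes 5 or 10 candidates that together explain 10 to 30% of residual variance, and conduct that the text permits but does not describe. What is at stake is the credibility of the primary p-value, particularly near 0.05. The endpoint, the design and the sample size are untouched. This should be fixed; it does not undermine the trial.

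**What to change.** - Remove baseline significance testing as a route into any model, and make the baseline table descriptive, without p-values.
- Fix the primary model as treatment, baseline QIDS-SR, the minimisation factors and GAD-7, plus any further covariates that are named and locked before outcome data are seen by arm. Name here the predictors of missing data on which the complete-case analysis relies. They can be looked for with the arms pooled.
- Replace the sentence on examining other covariates with one that confines any other adjustment to a labelled sensitivity analysis.

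The cost is a change of wording and an early decision on the predictors of missing data. The target stays at 290, because the sizing used an unadjusted t-test. No extra participants or data are needed.

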### Objectives and measures

A key design feature of the PAX-BD study is that outcome measures are mainly collected remotely, mostly using self-report tools implemented on-line using the True Colours platform [32]. Three scales, the Quick Inventory for Depressive Symptomatology – Self Report (QIDS-SR) [33], Altman Self-rating Scale of Mania (ASRM) [34] scale and Generalised Anxiety Disorder-7 (GAD-7) [35] scale are completed on-line by participants weekly from recruitment into the pre-randomisation phase through to the end of follow up. To facilitate comparison of PAX-BD with other studies, the clinician-rated version of the QIDS (QIDS-C) [33], the Montgomery-Asberg Depression Rating Scale (MADRS) [36] and the Young Mania Rating Scale (YMRS) [37] are completed by phone by the study Research Assistants (RAs) at two time points. The timings of the administration of assessments is shown in the Schedule of Events (Table 1).

**Table 1 Tab1:** Schedule of Events

	Screening	Pre-randomisation	Screening and Randomisation	0	Treatment weeks (Post-randomisation)																												Tapering (5, 6, 7)	
					1	2	3	4	5	6	7	8	9 to 11	12	13 to 15	16	17 to 19	20	21 to 23	24	25 to 27	28	29 to 31	32	33 to 35	36	37 to 39	40	41 to 43	44	45 to 47	48	49 to 51	52*
Informed consent (1,2)	✓		✓																															
Demographics	✓	✓																																
Eligibility assessment	✓		✓																															
Randomisation			✓																															
RA safety monitoring call (3, 8)		✓		✓	✓	✓	✓	✓	✓	✓	✓	✓	✓	✓		✓		✓		✓		✓		✓		✓		✓		✓		✓	✓	✓
CSO contact (4)						✓				✓				✓						✓						✓						✓		✓
QIDS-SR, GAD-7 and ASRM		✓		✓	✓	✓	✓	✓	✓	✓	✓	✓	✓	✓	✓	✓	✓	✓	✓	✓	✓	✓	✓	✓	✓	✓	✓	✓	✓	✓	✓	✓	✓	✓
SHAPS				✓						✓				✓																				
WSAS				✓						✓				✓						✓						✓						✓		
TSQM										✓				✓		✓		✓		✓		✓		✓		✓		✓		✓		✓		
QUIP-RS				✓						✓				✓		✓		✓		✓		✓		✓		✓		✓		✓		✓		✓
MADRS, QIDS-C and YMRS				✓										✓																				
IMP Dispensings			✓					✓						✓				✓				✓				✓				✓				
Qualitative Interviews		✓												✓																				
Participant Vouchers														✓												✓								✓
Unblinding (9)																																✓		

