### Secondary safety and acceptability objectives

To examine risk of switching to mania and occurrence of psychosis or impulse control disorders, which are known possible side-effects of pramipexole [24], over 48 weeks. Manic symptoms are assessed weekly using an on-line version of the ASRM scale [34]. Rates of impulsivity during the study are monitored using the Questionnaire for Impulsive-Compulsive Disorders in Parkinson’s disease – Rating Scale (QUIP-RS) [40], administered by telephone by the study RAs. Psychosis is not formally rated but is specifically screened for during regular RA phone calls.To examine side effects and overall acceptability of pramipexole treatment over 48 weeks using the Treatment Satisfaction Questionnaire for Medication (TSQM) [41] administered by phone by the study RAs.To examine tolerability of pramipexole by reviewing the rates, severity, seriousness, causality and expectedness Adverse Events (AEs) and Adverse Reactions (ARs).To examine adherence to medication over 48 weeks. Medication is provided to participants by post from the Cumbria, Northumberland, Tyne and Wear (CNTW) pharmacy on seven occasions over the course of the study. Adherence is assessed through a pill count of un-used medication returned by participants at the end of each prescription period.

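### Remission, response and depression-free time rest on QIDS-SR alone; same-week joint QIDS-SR and ASRM versions should be reported beside them

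*Protocol article*

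**What the plan says.** The definitions are in the protocol article, Statistical analysis. One secondary outcome is "the proportion of participants in remission at 12 and 48 weeks (QIDS-SR score ≤ 5", and the bracket closes there with no further condition. Another is "the proportion of participants who have achieved a response at 12 and 48 weeks", with response set as a QIDS-SR reduction of at least 50% from baseline. A third is the "proportion of time over 48 weeks that participants are free of depressive symptoms", again at QIDS-SR ≤ 5.

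Mania has its own entry in the same list: the "proportion of time over 48 weeks that participants are free of manic symptoms", at ASRM ≤ 5. The section also has weekly ASRM scores examined in the same way as weekly QIDS-SR, and YMRS analysed between weeks 0 and 12.

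Under Secondary safety and acceptability objectives, one aim is "To examine risk of switching to mania and occurrence of psychosis or impulse control disorders, which are known possible side-effects of pramipexole", over 48 weeks. Under Objectives and measures, QIDS-SR, ASRM and GAD-7 "are completed on-line by participants weekly from recruitment into the pre-randomisation phase through to the end of follow up".

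No outcome in the article requires a low QIDS-SR and a low ASRM together. No rule says how a participant who has switched is classified for remission or response.

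**The concern.** In bipolar disorder a depression score can fall because the participant has recovered or because the participant has changed pole. The three QIDS-SR outcomes do not separate these two routes, and the protocol itself regards the second as a possible effect of the drug.

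If pramipexole produces more switches than placebo, and some of those who switch score low on QIDS-SR, then remission, response and depression-free time all move in its favour for a reason that is not recovery. The word remission, used without qualification in a bipolar trial, is the label most likely to be misread. What is at stake is the interpretation of these secondary outcomes. The primary analysis, QIDS-SR at week 12 by ANCOVA, keeps its definition.

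**Working it through.** **1. Classification under the stated rules.** Take one weekly assessment with QIDS-SR 4 and ASRM above 5.

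- Remission (QIDS-SR ≤ 5): counted as remitted.
- Depression-free time: the week counts.
- Response: counted if the baseline QIDS-SR was 8 or more. Every randomised participant meets this, since entry requires QIDS-SR > 10.
- Mania-free time (ASRM ≤ 5): the week does not count.

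The time outcomes place the same week on opposite sides and are never joined. Remission and response have no mania counterpart at all.

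**2. The denominator, from the plan's own figure.** Inputs from Sample size, power and effect size: difference 3, SD 7, two-sided 5%, power 90%, dropout 20%.

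- Normal approximation: n per arm = 2 × (1.960 + 1.282)² × 7² / 3² = 114.4, so 115. With the exact t distribution it is 116.
- 2 × 116 / (1 − 0.20) = 290, the stated figure.
- Expected completers at week 12: 145 × 0.80 = 116 per arm. The primary analysis is complete-case and the secondary outcomes follow it, so 116 is the relevant count rather than the 145 randomised.

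**3. Size under an assumed excess.** The document gives no rate for switching, for remission, or for the joint state QIDS-SR ≤ 5 with ASRM > 5. All rates here are assumptions. If the joint state is 5 percentage points more common on pramipexole at week 12 (for example 8% against 3%), the QIDS-SR-only remission difference is 5 points larger than the difference in remission without manic symptoms. That is 0.05 × 116 = 5.8 participants. Assumed pairs of 5% against 3% and 12% against 4% give 2 and 8 points.

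**4. What this could do to a test.** Suppose remission without mania is equal in both arms at e, a share s of each arm has switched, and a fraction f of those score QIDS-SR ≤ 5. QIDS-SR-only remission is then e + f × s, and the apparent difference is f × (s on pramipexole − s on placebo).

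| e | s placebo | s pramipexole | f | Apparent remission, placebo / pramipexole | Difference | Chance of significance favouring pramipexole |
|---|---|---|---|---|---|---|
| 30% | 3% | 6% | 0.5 | 31.5% / 33.0% | 1.5 points | 4.3% |
| 20% | 3% | 10% | 1.0 | 23.0% / 30.0% | 7 points | 22.5% |
| 20% | 5% | 15% | 1.0 | 25.0% / 35.0% | 10 points | 38.2% |

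The chance is that of an unadjusted two-proportion test with 116 per arm: Φ[(difference − 1.96 × SE₀) / SE₁]. For the last row SE₀ = √(2 × 0.30 × 0.70 / 116) = 0.0602 and SE₁ = √((0.25 × 0.75 + 0.35 × 0.65) / 116) = 0.0598. This gives Φ(−0.30) = 0.38. With no difference it would be 2.5% in that direction.

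**5. Whether the two time outcomes already contain the answer.** If a share D of time is depression-free and a share M is mania-free, time free of both lies between max(0, D + M − 1) and min(D, M). With assumed margins:

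- D = 30%, M = 90%: 20% to 30%.
- D = 40%, M = 85%: 25% to 40%.
- D = 50%, M = 80%: 30% to 50%.

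In the middle case two arms could report identical values on both outcomes and still differ by up to 15 points in time free of both. The joint state has to be tabulated from the weekly data.

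**The case against.** The strongest reply is that each outcome measures what its name says. Depression-free time at QIDS-SR ≤ 5 is an accurate label, and the protocol does not present it as time well or as treatment success. The primary objective is effectiveness over 12 weeks on the QIDS-SR, and mania is deliberately placed under safety. Keeping benefit and harm apart is a recognised choice. All of this stands.

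A reader might infer that the plan overlooks mania or could not reveal it. The documents do not support that. Mania-free time, weekly ASRM, YMRS over 12 weeks and an explicit switching objective would show an excess. WSAS and EQ-5D-5L over 48 weeks are not tied to one pole.

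There is also a cap for the time outcome. Time with QIDS-SR ≤ 5 and ASRM > 5 cannot exceed total time with ASRM > 5, which is the complement of a planned result. If ASRM > 5 proves rare, any distortion of depression-free time is small. All randomised participants must also be on a mood stabiliser. The cap limits the concern without removing it: it leaves the wide range in step 5 when ASRM > 5 is not rare, and no remission or response outcome at week 12 or 48 has a matching ASRM proportion.

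The analysis plan is not shown and may add a joint outcome. The point therefore concerns only what the article fixes with numerical cut-offs. Finally, ASRM > 5 on one weekly self-rating marks manic symptoms, not a confirmed switch. That is a good reason not to replace the stated outcomes with joint ones.

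**Conclusion.** The point holds as a low-cost improvement to secondary outcomes. On the stated definitions a participant with QIDS-SR ≤ 5 and ASRM > 5 in the same week is in remission, and the separately reported mania results neither change that classification nor yield the time free of both poles.

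A reader might go further and infer that the remission comparison is biased by some known amount, or that the efficacy conclusion is unsafe. Neither follows. The document gives no switch or remission rates. The 5-point figure (about 6 of 116 completers), the 2 to 8 point range and the 1.5 to 10 point scenarios are all assumptions. The direction favours pramipexole only if the joint state is more common in that arm. The primary outcome definition, the sample size of 290 and its power are unaffected.

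**What to change.** Keep remission, response and depression-free time as stated, for comparability with other trials. Add, before unblinding, versions that use the protocol's own ASRM cut-off:

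- remission at 12 and 48 weeks: QIDS-SR ≤ 5 and ASRM ≤ 5 at the same weekly assessment;
- response at 12 and 48 weeks: QIDS-SR reduction of at least 50% from baseline and ASRM ≤ 5 at that assessment;
- proportion of weeks over 48 weeks with QIDS-SR ≤ 5 and ASRM ≤ 5.

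Report each beside its depression-only counterpart, by arm, so that a remission or response benefit can be separated from a change of pole. State how a week with only one of the two scales completed is handled.

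The cost is wording, a few more secondary analyses and that missing-scale rule; both scales are already completed weekly. Joint rates will be somewhat lower than the depression-only rates, and the report should say that ASRM > 5 denotes manic symptoms rather than a confirmed switch.
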